### Data safety and management

Data will be managed using Research Electronic Data Capture (REDCap; Vanderbilt University, Nashville, USA). This will be collected by well-trained research assistants using secure password-protected tablet computers with Research Electronic Data Capture (REDCap; Vanderbilt University, Nashville, USA). All paper case report forms or source documents will be filed and stored in lockable designated cabinets and rooms. To protect participants’ confidentiality all data will be identified by anonymized study numbers. Only authorized study staff, e.g., those that collect data in the clinics will have the possibility to link the anonymized information to other participant identifiers. The data will be stored in password-protected database with no participants’ identifying information. Designated study team members will have exclusive rights to the database. Database access for other members of the study team will be determined by their responsibilities on the study, e.g., data entry, query resolution, and data monitoring. For this study, we will capitalize on single data entry. Majority of the range and consistency checks will be inbuilt into the REDCap software. In addition, the study data manager will run routine consistency checks on the study data using STATA version 15 software. At publication of the findings of this study, no identifying information will be used.

ACCESS will serve as the study coordinating center and be responsible for training, regulatory oversight, data management, and community engagement. The coordinating center will be responsible for daily operations including data collection, the training of field workers and community health workers, and participant enrollment. The study team at the coordinating center will be comprised of the project manager, the study biostatistician, and the study physician. The trial steering committee will meet every 2 weeks. This committee is comprised of the principal investigator, project manager, co-investigators, and study statistician. This team will review enrolment and study endpoints. In addition, a stakeholder and public group will be part of this study. This will comprise a community advisory board of community leaders, health works, and Ministry of Health officials. The community advisory board will meet quarterly. The PI will present the study updates as well as obtain input from the community advisory board regarding community concerns.

The composition of data monitoring committee (DMC) is as follows: we intend to have a DMC comprising of an experienced clinician, statistician, and epidemiologist. The DMC will help to ensure that the procedures are in place to ensure efficient reporting for later analysis (data processing issues to ensure the quality and efficient reporting of the data, and check compliance with the protocol by those involved in the study). Therefore, we intend to have the first meeting of the DMC at 4 months from the study start date and another meeting at 8 months post study start.

### Data monitoring

We will conduct an interim analysis at 12 months to assess differences between groups. If a statistically significant difference is detected, the intervention will be applied across the remaining clusters. We do not have any pre-defined termination rules as this is a pragmatic study with minimal risks. As such, we do not have a data and safety monitoring (DSMB) or formal termination rules as determined by the local institutional review board (IRB). Should a participant have any complaints, these will be reported to the DMC.

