### Study design

The study will employ a closed cohort, superiority stepped wedge cluster randomized design. There will be a sequential crossover of clusters from the control to the intervention arms and the order of the cross over will be randomly determined (Fig. 1). This study will be conducted in 21 clusters within Nakaseke district. Each cluster will consist of 4–5 villages (Table 1). Participant recruitment will occur before randomization. At the beginning of the study period, we will collect baseline demographic data from each of the participants. All the villages within the study will eventually receive the intervention, thereby improving equity and acceptability. To minimize contamination, we will ensure that clusters are well separated to minimize social contact between participants in the intervention and control arms. Since all clusters will be observed under both the intervention and control arm, we anticipate that imbalances are less likely to occur. To further address the issue of contamination, individuals within the same cluster will be randomized to receive the intervention at the same time. Also, since the study will be conducted in a rural population, we expect adjacent neighborhoods to be far apart from each other, and this could additionally reduce the rates of contamination within the study area. In addition, CHW activities are directed to individuals at the level of the home and not large community groups or gatherings. This should decrease exposure of non-enrolled patients from outside randomized clusters to the interventions. We plan to rollout the intervention in two clusters per month and one cluster in the final month (Fig. 2).

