## Discussion

We discuss the rationale, methods, and protocols for the CHW-HTC closed cohort stepped wedge cluster randomized trial in Uganda. The overall goal of the trial is to evaluate the effectiveness of a CHW-led intervention in blood pressure control among confirmed hypertensive patients in a rural Ugandan community. Based on our statistical power calculations, we will work with a fixed number of 21 clusters, enrolling 40 participants in each cluster. Similar studies have proven applicability across various settings, strengthening our theory-informed approach. A number of studies show that CHWs can be effective in delivering patient management strategies. A randomized controlled trial based in Nepal proves that a female community health worker intervention could effectively reduce mean systolic blood pressure in hypertensive patients [26]. A Mexican-based study indicates that a CHW-led intervention among hypertensive or diabetic patients is associated with a twofold increase in the odds of disease control [27]. Similarly, a CHW-led intervention in the USA to improve hypertension management among Filipino Americans with uncontrolled blood pressure finds that blood pressure was controlled at a significantly greater percentage among the treatment group participants (83.3%) compared to the control group (42.7 %) [21].

We will follow 11 phases of implementing the intervention, introducing it within two clusters at each step of the trial and within one cluster in the final step (Fig. 2). Clusters will be assigned randomly to intervention rollout while one CHW will be attached to each cluster. We will center our intervention on monthly pro-active household visits by trained CHWs over a study period of 1 year. A local non-government organization and a multinational research group with wide-ranging experience in conducting research in rural communities will carry out the study. The local coordination will support overcoming economic and cultural barriers to enrollment and support the establishment of community trust. This clinical trial builds upon previous research and collaborations in LMIC settings investigating the advantages of engaging CHWs in the patient-centered management of hypertension.

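### On the stated rollout the 12-month interim rule has no clusters left to act on, and if its clock starts earlier it becomes an efficacy trigger with no stated boundary

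*Protocol article*

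**What the plan says.** Data monitoring schedules an interim comparison of the groups at 12 months, without saying from what date the months are counted. The consequence of a positive result is stated: "If a statistically significant difference is detected, the intervention will be applied across the remaining clusters". The same section then says "We do not have any pre-defined termination rules" and explains this by the pragmatic, low-risk nature of the study. It gives no interim significance level, no boundary and no effect on the final test.

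The rollout is described consistently. Study design says "This study will be conducted in 21 clusters within Nakaseke district" and "We plan to rollout the intervention in two clusters per month and one cluster in the final month". Sample size determination repeats that pace, Clustering and randomization assigns the clusters to eleven phases, and the Discussion says "We will follow 11 phases of implementing the intervention".

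Two further statements bear on timing. The Discussion places the monthly visits "over a study period of 1 year", while the Abstract and the Intervention section give a year as the duration of the visits. On oversight, Data safety and management says "we intend to have the first meeting of the DMC at 4 months from the study start date and another meeting at 8 months".

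**The concern.** A rule that moves the waiting clusters to the intervention needs clusters that are still waiting. On the article's own schedule there are none at 12 months if the count starts with the rollout. The look would then change nothing in the conduct of the trial, but it would still be a significance test ahead of any later final analysis.

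If the count starts earlier, some clusters could still be in control. A significant result would then move all of them at once, and no concurrent control data would accrue afterwards. That works as an efficacy stop for the randomised comparison, whatever it is called. With no boundary stated, the false-positive rate of the trial is not fixed by what is written.

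The length of the study adds to the problem. If the whole study lasts one year, month 12 is its end and not an interim. If each cluster receives a year of visits, the last cluster finishes at about month 11 + 12 = 23. The article does not settle which analysis is the final one.

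**Working it through.** **Inputs from the protocol article.** 21 clusters; two crossing each month and one in the last month; eleven phases; interim at 12 months with origin unstated; 40 participants per cluster; blood pressure at baseline and every 3 months (Abstract). The significance level in Sample size determination is printed as 0.05%, presumably a slip for 0.05.

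**Assumptions, because the article does not give them.** ICC 0.01 to 0.10 (0.01 and 0.05 in the lagged schedules); within-person share of the remaining variance 0 or 0.5; follow-up to 24 months; two-sided 5% at each look. The outcome SD is not given either, but it cancels from the ratio of informations.

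**Step 1: the plan's own figure.** 10 × 2 + 1 × 1 = 21 clusters in 10 + 1 = 11 monthly phases. Cumulative crossovers are 2, 4, 6, …, 20, 21. The stated eleven phases are reproduced, and the last cluster crosses in month 11.

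**Step 2: clusters still in control at month 12.** If rollout starts L months after the 12-month clock, the number remaining is 21 − min(21, 2 × (12 − L)).

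- L = 0: 2 × 12 = 24, capped at 21; 0 remain
- L = 1: 2 × 11 = 22, capped at 21; 0 remain
- L = 2: 21 − 20 = 1
- L = 3: 21 − 18 = 3
- L = 4: 21 − 16 = 5
- L = 6: 21 − 12 = 9

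The rule has something to act on only if the clock starts at least two months before rollout.

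**Step 3: type I error if clusters do remain.** With information fraction t at the look, the two test statistics have correlation √t under the null. The overall error is 1 − P(|Z₁| < 1.96 and |Z₂| < 1.96). The fractions come from a closed-cohort stepped-wedge linear mixed model with 11 sequences, 3-monthly measures, and month 12 set against month 24.

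- Lags of 2 to 4 months: t about 0.80 to 0.90, overall error about 6.5% to 7.1%
- Lag of 6 months: t about 0.69 to 0.74, overall error about 7.4% to 7.6%

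If the printed 0.05% is taken literally at both looks, the overall error is about 0.07% to 0.09%, which is again above nominal.

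**Step 4: information lost if all remaining clusters cross at month 12.** Under the same model the loss is nil at lags of 2 to 4 months, because the 3-monthly measurement grid does not register the change. At a 6-month lag it is about 18% to 19%.

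**The case against.** The case on the other side is substantial in several respects.

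- **Origin.** The article gives no origin for the 12 months, recruitment comes before randomisation, and the enrolment and assessment schedule is a figure that is not shown. A reader might conclude that the rule can never work. The documents support only that it is empty when counted from rollout or from one month before. This part of the objection stands.
- **Interim level.** No interim level is stated, and alpha and boundary are commonly left to an analysis plan or full protocol that is not at hand. An unadjusted 5% look is therefore an assumption and cannot be presented as the plan's rule. This also stands. It does not rescue the stated action, which is either empty or an efficacy trigger.
- **Termination rules.** The denial of termination rules can be read as concerning safety, since it is justified by minimal risk. That is a fair reading. Even so, an action triggered by efficacy significance sits badly beside a general denial in the same section.
- **Oversight.** A reader might infer that no independent body would see the look and that unblinded investigators inspect results every fortnight. The text does not go that far. Two DMC meetings are named without saying that there are no others. Of the steering committee it says "This team will review enrolment and study endpoints", without mentioning results by exposure status. No reviewer is named for the 12-month look. These inferences are not part of the point.
- **Size.** An error of 8.3% would need an information fraction of 0.5. No modelled schedule comes near that, so this figure is not claimed.

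**Conclusion.** The point holds in conditional form. On the stated schedule all 21 clusters have crossed over by month 11, so a 12-month rule about waiting clusters has no object when the count starts at rollout or one month before it. This part is arithmetic on the article's own numbers.

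If the count starts two or more months before rollout, the rule is an efficacy-triggered end to concurrent control with no stated boundary. An overall error of about 6.5% to 7.6% in place of 5% then rests on an unadjusted two-sided 5% at both looks, the assumed ICC and within-person correlation, and 24 months of follow-up. Control data already collected would stay usable. The loss of information is nil in the model at lags of 2 to 4 months and reaches 18% to 19% only at 6 months.

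A reader might also infer that month 12 should simply become the final analysis. The documents do not support that. The last cluster would have about one month of exposure, against a year of planned visits and an analysis that treats exposure time as an effect modifier.

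Both readings leave a defective rule, so it should be resolved before any 12-month analysis is run.

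**What to change.** Preferred: delete the interim significance test and its crossover action. State that there is one primary analysis, at the full two-sided 5%, at the end of planned follow-up, and correct the printed 0.05% if it is a slip.

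Alternative, if a look is wanted:

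- Define its time origin so that it falls while clusters are still in control. The DMC meeting 8 months after study start would qualify: if rollout begins at study start, 21 − 2 × 8 = 5 clusters are still waiting, and more if it begins later.
- Use a Haybittle-Peto or O'Brien-Fleming boundary, with the final test adjusted to match.
- Have the DMC review it, and extend the DMC's remit accordingly, since the article describes that remit as data quality, reporting and protocol compliance.
- Reword the statement on termination rules so that it agrees with the look.

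In either case, reconcile the one-year study period in the Discussion with the year of visits in the Abstract and the Intervention section, so that the time of the final analysis is clear.

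Cost: wording in the protocol and analysis plan. Deleting the rule leaves the sample size unchanged. Keeping a look under one of these boundaries costs a very small amount of power.

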### Risks

This is a minimal risk study. The only intervention provided is education delivered by CHWs. As this is a pragmatic trial, the only adverse events anticipated are limited but not exclusive to a risk of loss of confidentiality, inordinate amount of participant time spent answering questions or participating in educational activities, or infections following a finger stick glucose screening. Because of the low risk, a formal DSMB will not exist, and we do not have formal termination rules as determined by the local IRB. Any potential adverse events will be reviewed by the trial steering committee and reported to the DMC. In addition, participants may experience discomfort from measuring devices such as sphygmomanometer when blood pressure is measured. Furthermore, some participants may feel uncomfortable sharing their personal information such as medical histories. Should a participant have any complaints, these will also be reported to the DMC.

### Benefits

There is no direct monetary benefit for participants. The project will generate data for the Ugandan Ministry of Health necessary to inform policy on improving treatment outcomes among hypertensive patients.

### Dissemination plan

We plan to disseminate results to the beneficiaries, Makerere University College of Health Sciences, Uganda Initiative for Integrated Management of Non-Communicable Diseases (UINCD), and the Ugandan Ministry of Health, with particular interest to the NCD directorate. Additionally, we will disseminate through quarterly reports, national and international conferences, and publication(s) in a peer reviewed journal, as well as press conferences and website displays.

## Discussion

We discuss the rationale, methods, and protocols for the CHW-HTC closed cohort stepped wedge cluster randomized trial in Uganda. The overall goal of the trial is to evaluate the effectiveness of a CHW-led intervention in blood pressure control among confirmed hypertensive patients in a rural Ugandan community. Based on our statistical power calculations, we will work with a fixed number of 21 clusters, enrolling 40 participants in each cluster. Similar studies have proven applicability across various settings, strengthening our theory-informed approach. A number of studies show that CHWs can be effective in delivering patient management strategies. A randomized controlled trial based in Nepal proves that a female community health worker intervention could effectively reduce mean systolic blood pressure in hypertensive patients [26]. A Mexican-based study indicates that a CHW-led intervention among hypertensive or diabetic patients is associated with a twofold increase in the odds of disease control [27]. Similarly, a CHW-led intervention in the USA to improve hypertension management among Filipino Americans with uncontrolled blood pressure finds that blood pressure was controlled at a significantly greater percentage among the treatment group participants (83.3%) compared to the control group (42.7 %) [21].

We will follow 11 phases of implementing the intervention, introducing it within two clusters at each step of the trial and within one cluster in the final step (Fig. 2). Clusters will be assigned randomly to intervention rollout while one CHW will be attached to each cluster. We will center our intervention on monthly pro-active household visits by trained CHWs over a study period of 1 year. A local non-government organization and a multinational research group with wide-ranging experience in conducting research in rural communities will carry out the study. The local coordination will support overcoming economic and cultural barriers to enrollment and support the establishment of community trust. This clinical trial builds upon previous research and collaborations in LMIC settings investigating the advantages of engaging CHWs in the patient-centered management of hypertension.

Currently, CHW-interventions focus on the management of infectious diseases such as malaria, tuberculosis, or HIV. In addition, few studies have evaluated the impact of CHWs in NCD management such as hypertension in rural and urban settings. While these interventions have proven successful, evidence on the health outcomes of employing CHWs in a rural Ugandan setting and in the management of NCDs is limited. Hence, findings from this study will optimize disease detection and referral in rural Uganda. Furthermore, they will provide evidence-based policy recommendations on a regional and national scale. If successful, this trial has the potential to change the way we understand CHW interventions for the management of NCDs in Uganda. This may benefit patients in countries with similar socio-economic contexts by making hypertension treatments more accessible for rural communities.

## Data Availability

The datasets analyzed during the current study and statistical code are available from the corresponding author on reasonable request, as is the full protocol.

## Abbreviations

ACCESS: African Community Centre for Social Sustainability
BMI: Body mass index
CHWs: Community health workers
COPD: Chronic obstructive pulmonary disease
DSMB: Data and safety monitoring board
FBS: Fasting blood sugar
IRB: Institutional review board
LMICs: Low- and middle-income countries
MCID: Minimally important clinical difference
MOH: Ministry of Health
NCDs: Non-communicable diseases
NIH: National Institute of Health
PI: Principal investigator
RBS: Random blood sugar
SSA: Sub-Saharan Africa
WHO: World Health Organization
WHO PEN: Package of Essential Non-Communicable Diseases Interventions
